#### Questionnaires

The participants will respond to a questionnaire containing 6 questions about the self-perception of the emotional state besides the utility and truthfulness of messages, as detailed in Table 1.

Furthermore, as it is expected that age, levels of education, electronic health literacy, and oral health knowledge can influence the ability of participants in acquiring and criticizing digital content [25,26]; these outcomes will be determined through specific questionnaires.

eHealth literacy is defined as the ability of a person to search, find, understand, and evaluate digital health information and apply the acquired knowledge to address or solve a health issue [27]. It will be measured by the Brazilian version of the eHealth Literacy Scale (eHEALS) [28]. This instrument consists of 8 items linked to the consumption of health information on the internet, as demonstrated in Textbox 1. Participants must answer each question according to their self-perception using a 5-point Likert scale that has options varying from “completely agree” to “completely disagree,” with a total score ranging between 8 and 40 points [28].

The participants’ oral health knowledge will be assessed using the questionnaire proposed by Vilella et al [29], which measures knowledge related to topics of interest in pediatric dentistry, such as breastfeeding, sugar intake, bottle feeding, oral hygiene, and use of fluoride toothpaste (Textbox 2). Questions will be answered using a 3-point Likert scale, categorized as “completely agree,” “neither agree nor disagree,” and “completely disagree.” It should be noted that only the “completely agree” option is precise. Hence, the participants receive a point for each correct answer, with a final score ranging between 0 and 9.

Moreover, the participants will answer questions about their sociodemographic characteristics, self-perception of their oral and general health, and use of internet-based health information.

**Table 1 table1:** Questionnaire about self-perception of the emotional state of participants, as well as the utility and truthfulness of messages after the consumption of fluoride-related content.

Question category		Answer options

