## Introduction

Dental caries in children is still a significant public health challenge in distinct populations, affecting 532 million infants worldwide, mainly in socially disadvantaged families [1,2]. Its contemporary management focuses on improving personal dietary and oral hygiene habits, as it is a sugar- and biofilm-driven disease resulting from consecutive dental demineralization processes [2,3]. In this context, fluoride-containing oral care products and drinking water play an important role in preventing dental demineralization and promoting remineralization [4-6]. Nevertheless, false or misleading content on the internet continually propagates the discouragement of fluoride usage because of possible adverse health effects [7], which supports the development of dental beliefs that could negatively impact parental oral health behaviors [8]. At the same time, fluoride refusal is a growing concern observed in pediatric dental offices, probably driven or reinforced by internet-based disinformation [9].

Indeed, diverse aspects such as innovative messages, information overload, and predisposed personal characteristics such as pre-existing beliefs, ideological motivations, and political polarization influence the spread of false or misleading web-based content [10-13]. Concurrently, digital users tend to interact with posts associated with their interests uncritically, reinforcing the emergence of echo chambers on social media [13-15]. On the other hand, people may also be susceptible to persuasive information slightly misaligned with their current motivations and behaviors (eg, falsehoods formulated to deceive called disinformation) [16,17]. This process of cognitive dissonance can cause different emotional reactions starting from discomfort or stress to a counterreaction depending on the threat to the individual’s freedom, a response known as psychologic reactance [16,18,19]. Interestingly, people with motivations more aligned to the values of persuasion messages exhibit less physiological arousal than less-aligned individuals [16]. Additionally, American adults likely to believe in conspiracy theories have more stressful life events and more significant perceived stress [20]. Nevertheless, the users' emotional reactions during the consumption of internet-based oral health information and disinformation remain uncertain.

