**Truthfulness**		
	5. Have you already read or heard about these messages before this research?	Yes
		No
	6. How do you classify most of these messages?	True
		False

Brazilian version of the eHealth Literacy Scale questionnaire presented in English.I know how to find helpful health resources on the Internet.I know how to use the Internet to answer my questions about health.I know what health resources are available on the Internet.I know where to find helpful health resources on the Internet.I know how to use the health information I find on the Internet to help me.I have the skills I need to evaluate the health resources I find on the Internet.I can tell high-quality health resources from low-quality health resources on the Internet.I feel confident in using information from the Internet to make health decisions.

Questionnaire about oral health knowledge of parents or caregivers.The child who is breastfeeding does not need to eat any other type of food until the six months old.Up to six months old, even breastfeeding, the baby also needs to ingest water.After six months old, the baby should eat foods other than maternal milk.After six months old, the baby should no longer drink breast milk.After one year, the baby can taste foods containing sugar.The best way to give teas and juices to babies is using a bottle.After six months old, the baby can be bottle-fed overnight or as much as you want.While the child has baby teeth, it should wear a piece of diaper moistened with filtered water for clean teeth.Babies under two years of age can use the same toothpaste as the adults.Note: Questionnaire proposed by Vilella et al [29] 

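### The printed scoring rule credits only agreement on all nine oral health knowledge items, although the items are worded in opposing directions; an item-by-item key is needed.

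*Protocol article*

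**What the plan says.** The Questionnaires section of the protocol article adopts an existing instrument for oral health knowledge. On the response format it says "Questions will be answered using a 3-point Likert scale", the options being agreement, a neutral middle and disagreement. It then says that "only the “completely agree” option is precise" and draws the scoring from that: "the participants receive a point for each correct answer, with a final score ranging between 0 and 9". No item is excepted and no reverse scoring is mentioned.

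Textbox 2 prints the nine statements. Four show how the direction changes:

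- Item 1: "The child who is breastfeeding does not need to eat any other type of food until the six months old"
- Item 2: "Up to six months old, even breastfeeding, the baby also needs to ingest water"
- Item 4: "After six months old, the baby should no longer drink breast milk"
- Item 7: "After six months old, the baby can be bottle-fed overnight or as much as you want"

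Item 3, placed before item 4, says that foods other than breast milk should be given from the same age. Items 5, 6 and 9 are, like item 7, permissive statements (sugar, bottles, toothpaste).

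The Outcomes section lists the score among the secondary outcomes and as a possible confounder of the primary ones. The statistical paragraph admits factors to the multiple logistic models by a Wald screen at P<.2. Principal Findings in the Discussion expects younger adults with more eHealth literacy and knowledge to be less persuaded by disinformation.

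**The concern.** A knowledge score has to rise with knowledge. Under one key for all items it does so only if the knowledgeable answer is the same throughout. Here the statements pull in different directions on the same subject, yet agreement earns the point every time. The article does not merely leave the key to a fuller document; it states a key, and that key does not fit the items printed with it.

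If analysts apply the sentence as printed, informed parents lose a point on every item where they rightly disagree, and misinformed parents gain one. The relation of knowledge to the psychophysiological measures could then be diluted or carry the wrong sign. A reader testing the expectation in the Discussion could conclude the opposite of what the answers show.

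**Working it through.** **Inputs.** Nine items, one point each, agreement as the only scoring answer (Questionnaires and Textbox 2). The number k of items that should be keyed to disagreement is not in the documents. It is an assumption, shown over its full range.

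**The plan's own range.** 9 items × 1 point = 9 at most, and 0 at least. The stated range of 0 to 9 is reproduced.

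**Scores under the printed rule and under an item-by-item key**

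- Agrees with everything: 9 as printed; 9 − k with a correct key.
- Right on every item: 9 − k as printed; 9 with a correct key.
- Wrong on every item, with no neutral answers: k as printed; 0 with a correct key.

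The gap between fully informed and fully misinformed is therefore (9 − k) − k = 9 − 2k as printed, against 9 with a correct key. It is positive for k up to 4 and negative from k = 5.

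**Illustrative correlation.** 200,000 respondents were simulated with one standard normal knowledge trait, a logistic probability of a right answer that is the same for all items, and 15% neutral answers. All of these are assumptions. The last column is the correlation of the printed-rule score with the correctly keyed score.

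| k keyed to disagree | Fully informed | Fully misinformed | Gap 9 − 2k | Correlation |
|---|---|---|---|---|
| 0 | 9 | 0 | 9 | 1.00 |
| 1 | 8 | 1 | 7 | 0.90 |
| 2 | 7 | 2 | 5 | 0.75 |
| 3 | 6 | 3 | 3 | 0.54 |
| 4 | 5 | 4 | 1 | 0.25 |
| 5 | 4 | 5 | −1 | −0.06 |
| 6 | 3 | 6 | −3 | −0.35 |
| 7 | 2 | 7 | −5 | −0.58 |
| 8 | 1 | 8 | −7 | −0.75 |
| 9 | 0 | 9 | −9 | −0.87 |

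A separate simulation, also with a normal trait and logistic responses, gave 0.75, 0.52, 0.19, −0.19, −0.51 and −0.75 for k = 2 to 7. The sizes move with the response model. In both simulations the sign changes between k = 4 and k = 5, as the gap column requires without any simulation.

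**Where it enters the analysis.** The between-group comparison is a Student *t* test or Mann-Whitney *U* test, and no covariate is named for it. The knowledge score can enter only the multiple logistic models, and only after the P<.2 screen. A score that is exactly reversed would pass a two-sided Wald screen as often as a correct one and adjust equally well, but its coefficient would have the wrong sign. A partly mis-keyed score is noisier, so it can fail the screen wrongly or adjust poorly.

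**The case against.** The strongest reply is that the items do not strictly contradict one another. Item 1 is about food and item 2 about water; items 3 and 4 can both be affirmed; and item 7 does not mention sugar, so setting it against the Introduction's account of caries, "it is a sugar- and biofilm-driven disease resulting from consecutive dental demineralization processes", needs a premise about what is in the bottle. This stands. The documents make k = 0 implausible; they do not prove it impossible.

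Second, the sentence may be a loose translation, meaning perhaps that only a definite answer can score, and the cited questionnaire may carry its own key. That is possible, and it means the documents do not show that data will actually be mis-scored. It does not rescue the printed rule, which is what a reader or analyst would follow.

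Third, the damage is recoverable. The knowledge data are to be entered in spreadsheets and the raw data made openly available, so rescoring is possible if individual item answers are kept. This also stands, and it lowers the severity.

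A reader might go further and infer that the adjustment of the group effect is wrong and the trial's main result biased. The documents do not support that: groups are randomised and the main comparison uses no covariate. Nor do the calculations show that the score measures a habit of agreeing, since no such tendency was described in either simulation.

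**Conclusion.** The printed scoring rule does not fit the printed items. That an all-agree respondent reaches 9 of 9 follows directly from the text and rests on no assumption. Beyond that, the size depends on k, which the documents do not give. The score is sound only at k = 0, weakened for k of 1 to 4, and reversed for k of 5 or more. The simulated correlations are illustrations, not estimates for this trial.

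It is tempting to read a minimum k from the wording and say how much signal is lost. That would require deciding the right answer to individual feeding and hygiene items, which this review does not do.

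The consequence is limited to a secondary variable and candidate covariate: its descriptive summary, its P<.2 screening, its coefficient, and any test of the expectation in the Discussion. The randomised comparison of the primary outcomes stands. This should be corrected before the score is analysed, but it does not threaten the trial.

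**What to change.** Reconcile the Questionnaires section with Textbox 2. Replace the sentence on the single correct option with a table taken from the cited source questionnaire that states, for each of the nine items, whether full agreement or full disagreement earns the point. State that the neutral option scores 0. Enter and keep the item-level answers rather than totals alone, compute the 0 to 9 score from them, and recompute it for anyone already scored under the printed rule. Put the key beside the data in the public repository.

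The cost is nine key entries and a line of scoring code. No new data, visits or participants are needed. No clinical answer to any item is proposed here; the key should come from the source instrument.

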**Emotional state**		
	1. After consuming these messages, I am feeling...	Calm
		Hectic
	2. After consuming these messages, my feeling is...	Positive
		Negative
**Utility**		
	3. Are these messages useful for your own health or for your family's health?	Yes
		No
	4. Are these messages important to other people to make their health decisions?	Yes
		No
**Truthfulness**		
	5. Have you already read or heard about these messages before this research?	Yes
		No
	6. How do you classify most of these messages?	True
		False

Brazilian version of the eHealth Literacy Scale questionnaire presented in English.I know how to find helpful health resources on the Internet.I know how to use the Internet to answer my questions about health.I know what health resources are available on the Internet.I know where to find helpful health resources on the Internet.I know how to use the health information I find on the Internet to help me.I have the skills I need to evaluate the health resources I find on the Internet.I can tell high-quality health resources from low-quality health resources on the Internet.I feel confident in using information from the Internet to make health decisions.

Questionnaire about oral health knowledge of parents or caregivers.The child who is breastfeeding does not need to eat any other type of food until the six months old.Up to six months old, even breastfeeding, the baby also needs to ingest water.After six months old, the baby should eat foods other than maternal milk.After six months old, the baby should no longer drink breast milk.After one year, the baby can taste foods containing sugar.The best way to give teas and juices to babies is using a bottle.After six months old, the baby can be bottle-fed overnight or as much as you want.While the child has baby teeth, it should wear a piece of diaper moistened with filtered water for clean teeth.Babies under two years of age can use the same toothpaste as the adults.Note: Questionnaire proposed by Vilella et al [29] 

#### Outcomes

The primary outcomes will be obtained by comparing the psychophysiological reactions and self-reported emotional states of participants, as well as the self-perception of the utility and truthfulness of the content between the 2 groups.

The secondary outcomes will be related to sociodemographic characteristics, eHEALS scores, and oral health knowledge of the participants, and these are considered possible confounding factors of primary outcomes.

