Therefore, this study aims to evaluate the patterns of psychophysiological reactions of adults after the consumption of internet-based fluoride-related information and disinformation. The hypothesis (*H_1_*) for this randomized controlled trial indicates that there are differences in the psychophysiological reactions of adults exposed to oral health information and disinformation.

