Each slide will show a short and straightforward message (maximum of 200 characters) for 15 seconds, which is sufficient for the participants to read and understand it [23]. The slides will be developed with a white background and contain messages in black font. By default, the messages will be aligned at the center of the slides. Additionally, the messages will be related to the main issues that emerged from a previous characterization of false or misleading fluoride-related posts on social media [24]. In this regard, we will format the original content of false or misleading posts (intervention group) to ensure a better simulation of the digital environment. Despite the difficulties in classifying distinct information disorder types, the intervention group participants will only receive disinformation because they are intended to deceive individuals intentionally [17].

At the end of the experimental session, the same video used to collect baseline data will be made available to participants for an additional 150 seconds to measure the variations in the psychophysiological parameters.

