### Data Collection, Management, and Analysis

First, the HR data of the participants will be exported from Polar Ignite 2 and Polar Verity Sense to Microsoft Excel (Microsoft Corporation) as.csv files. Further, the sociodemographic, oral health knowledge, self-perception about information, and eHEALS data will be manually entered into Excel sheets. Moreover, the videos will be exported from the camera and stored in a closed repository for further analysis, according to the findings of Bevilacqua et al [31,32]. Notably, the features were designed based on previous reports regarding the potential to distinguish participants' emotional states [31-34]. As a result, 9 psychophysiological features will be calculated, with 7 related to facial activity and 2 to HR, as summarized in Table 2.

**Table 2 table2:** Description of the psychophysiological characteristics to be measured in the clinical trial.

Feature number	Facial landmark	Description
F_1_	Mouth outer	Monitor the zygomatic muscle
F_2_	Mouth corner	Monitor the zygomatic muscle
F_3_	Eye area	Monitor the orbicularis oculi muscle (eg, blinking)
F_4_	Eyebrow activity	Monitor the corrugator muscle
F_5_	Face area	Monitor facial movement to and away from the camera
F_6_	Face motion	Describe the total distance the head has moved in any direction in a short period
F_7_	Facial COM^a^	Describe the overall movement of all 68 facial landmarks
F_8_	Measured HR^b^	Measurement of HR using Polar Ignite 2 and Polar Verity Sense
F_9_	Remote HR	Estimated measurement of HR using the rPPG^c^ technique

^a^COM: center of mass.

^b^HR: heart rate.

^c^rPPG: remote photoplethysmography.

Features F_1_ to F_7_ are grounded on 68 facial landmarks automatically detected using constrained local neural fields (CLNFs) and are calculated using the Euclidian distance between those facial landmarks [31,32]. However, subjects have unique facial shapes and characteristics, which could prevent their comparison. Thus, we will first calculate a normalization coefficient for the Euclidian distance between the upper and lowermost anchor landmarks to mitigate this problem [31]. Additionally, feature F_9_ is based on remote estimations of HR performed using the established remote photoplethysmography  (rPPG) technique [35]. This is an extremely resilient technique when estimating the HR under challenging conditions and could be combined with the disinformation consumption scenario.

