Statistical analysis will be performed using Stata 17.0 software (StataCorp LLC, College Station, TX, USA). The questionnaire and psychophysiological data will be expressed through descriptive analysis (mean, SD, median, minimum, maximum, and percentage of variation). Moreover, the Shapiro-Wilk and Levene tests will be performed to analyze the normality and homogeneity of data to determine significant differences between groups by the Student *t* test (parametric analysis) or Mann-Whitney *U* test (nonparametric analysis). Further, multiple logistic regression models will be developed to evaluate the association of distinct variables with the psychophysiological aspects. Only factors with significant Wald statistics in the simple analysis will be included in the multiple models (*P*<.2). Furthermore, ROC curve analysis will be performed to determine the accuracy of F_9_ concerning F_8_. For all analyses, *P*<.05 will be considered statistically significant.

It is noteworthy that anonymized data will be shared in a public repository after the end of this study.

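### Nine features and six questionnaire items are all primary and each is tested at P<.05, so the 5% level does not apply to the trial's hypothesis (about 27–37% across the features at assumed correlations of 0.5 to 0)

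*Protocol article*

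**What the plan says.** - **Primary set.** Outcomes (Protocol article) states: "The primary outcomes will be obtained by comparing the psychophysiological reactions and self-reported emotional states of participants". Perceived utility and truthfulness of the messages belong to the same primary set. No member of this set is singled out.
- **How many features.** Data Collection, Management, and Analysis: "9 psychophysiological features will be calculated, with 7 related to facial activity and 2 to HR". Table 2 lists them as F1 to F9.
- **How many items.** Questionnaires section: "The participants will respond to a questionnaire containing 6 questions about the self-perception of the emotional state besides the utility and truthfulness of messages". Table 1 gives two items each for emotional state, utility and truthfulness, all with two answer options.
- **Test and level.** The analysis text will "determine significant differences between groups by the Student *t* test (parametric analysis) or Mann-Whitney *U* test (nonparametric analysis"), and "For all analyses, *P*<.05 will be considered statistically significant". The abstract and Trial Design state the same level.
- **Hypothesis.** The Introduction's H1 is that "there are differences in the psychophysiological reactions of adults exposed to oral health information and disinformation". Questionnaire answers are not part of it.
- **Windows.** Intervention describes a 150-second baseline, 25 messages of 15 seconds each, and a closing period in which "the same video used to collect baseline data will be made available to participants for an additional 150 seconds". The article does not say which window is compared between arms.
- **Sample size.** The 58 participants are argued from heart rate variability results of an earlier study. No other feature or item is mentioned there.

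**The concern.** H1 is broad and has nine routes to confirmation, each open at 5%. The primary set adds six further comparisons. Nothing ranks them, combines them or shares the error rate among them. A significance level of 5% protects one test. It does not protect a hypothesis that is accepted when any of several tests succeeds.

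The conclusion that disinformation changes how adults react could therefore rest on a single chance result among nine. The Conclusions intend the findings to support further studies and automatic detection tools, so a false lead would be carried forward.

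One item also sits oddly in the primary set. Item 5 asks whether the messages had been met before the study. That describes familiarity and is not a reaction to the content.

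**Working it through.** **Plan's own figure.** The protocol states no familywise error rate. Its only figure is 5% per test, which is right for one test: 1 − 0.95¹ = 0.05.

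**Inputs**
- Features bearing on H1: 9 (Table 2).
- Questionnaire items: 6 (Table 1), so 9 + 6 = 15 primary comparisons, counting each feature once.
- Level per test: 0.05, with no adjustment stated. Sidedness is not stated; two-sided is assumed.
- Correlation between outcomes: not given. Assumed range 0 to 0.5, with 0.9 as an extreme.
- Condition: no true difference on any outcome counted (the global null).

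**Independent tests.** Chance of at least one P<.05 among k tests = 1 − 0.95^k.
- Features: 1 − 0.95⁹ = 0.370
- All primary comparisons: 1 − 0.95¹⁵ = 0.537
- Items alone: 1 − 0.95⁶ = 0.265

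**Correlated tests.** Simulation of k two-sided z tests with one common correlation ρ, 400,000 draws, counting any |z| > 1.96:

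| ρ | 9 features (H1) | 15 comparisons (any primary finding) |
|---|---|---|
| 0 | 37% | 54% |
| 0.3 | 33% | 46% |
| 0.5 | 27% | 36% |
| 0.9 | 12% | 14% |

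**Uneven correlation.** Some features overlap by design: F1 and F2 both monitor the zygomatic muscle, and F8 and F9 both concern heart rate. An illustrative structure uses 0.8 for F1/F2, 0.9 for F8/F9, 0.5 among F5 to F7, 0.2 between other features, 0.3 among items, and none between features and items. It gives 31% for nine features and 48% for all 15.

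**Leaving out F9.** If F9 serves only to be validated against F8, the independent figures are 1 − 0.95⁸ = 0.337 and 1 − 0.95¹⁴ = 0.512.

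**Is 5% a fair level for two-option items?** With 26 or 29 per arm and a common proportion of 0.5, 0.7 or 0.9, the true level of the t test or the Mann-Whitney test on such an item is 3.9% to 5.5%. Counting each item at 5% is reasonable for the tests named.

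**What adjustment does.** Bonferroni across nine gives 0.05/9 = 0.0056 per test and 1 − (1 − 0.0056)⁹ ≈ 0.049. Across 15 it gives 0.05/15 = 0.0033 and again about 0.049. Holm keeps the same bound and is never less powerful.

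**Cost in power, by assumption only.** Take a standardized difference of 0.8, which is not in the protocol, and 26 per arm (58 × 0.9 = 52.2, so about 52 completers). The noncentral t has 50 degrees of freedom and noncentrality 0.8 × √(26/2) = 2.88. Power is 81% at 0.05, 50% at 0.05/9 and 43% at 0.05/15. The last two are the strictest Holm step, so power for a given feature under Holm is at least that.

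**The case against.** **The article is condensed, and multiplicity methods often stand in an analysis plan.** This would answer a document that was silent. This one is not: it names every domain as primary and sets P<.05 for all analyses. A later plan could control the error rate only by departing from that text.

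**The features are correlated, so independence overstates the error.** This stands, and independence is treated here as the upper figure. Even at a common correlation of 0.9 the rate is 12% for nine features, more than twice 5%.

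**The study is partly exploratory.** Its results are meant to support further work, which lowers the stakes. But it states a hypothesis and a significance level, and the two do not match.

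Four stronger readings are tempting, and the documents do not support them:
- *That 36–54% is the chance of falsely confirming H1.* H1 covers psychophysiological reactions only. A false difference on a utility or truthfulness item is a false primary finding, but it does not confirm H1.
- *That the features will be tested in both the exposure and the closing window, which would raise the count.* The closing video is there to measure variation, and percentage of variation is listed as a descriptive. No separate between-arm test per window is planned. The window is simply not fixed.
- *That mean heart rate is already the variable behind the sample size.* The Sample Size section cites heart rate variability, a different quantity.
- *That item 5 should be used as a covariate.* It is asked after exposure, about messages that differ by arm, and the Discussion names novelty as an expected source of the reaction. Adjusting for it could remove part of the effect.

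**Conclusion.** The point holds. All nine features and all six items are primary, each is judged at 5%, and nothing controls the error across them. With no true differences, the chance of at least one false difference that could be taken to confirm H1 is 37% if the features are independent, about 27% at a common correlation of 0.5 and 12% at 0.9. For any false primary finding among 15 the figures are 54%, 36% and 14%.

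These rest on assumed correlations, two-sided tests, one comparison per feature and the global null. The exact size is therefore uncertain, but no correlation examined brings it near the stated 5%. The level the trial quotes does not apply to its hypothesis.

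**What to change.** Change Outcomes and the statistical analysis text in one of two ways.

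1. **One primary outcome.** Name one psychophysiological feature in one stated window, tested at two-sided 5%. Measured heart rate (F8) during the message slides, adjusted for the 150-second baseline, is one possibility. Whichever is chosen should be justified as a choice and the sample size aligned with it, because the present argument cites heart rate variability.
2. **A primary family.** Keep the features as primary, state the window, and control familywise error across them with Holm.

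Under either option:
- Make the questionnaire items secondary, with Holm or false-discovery-rate adjusted P values. Under option 1, treat the remaining facial features the same way.
- Treat F9 as a validation measure against F8, outside the family that tests H1.
- Report item 5 descriptively by arm, not as a covariate.
- Limit the general P<.05 sentence to the primary analysis, or to adjusted P values.

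**Cost.** Wording and a small change of analysis; no new data. Fewer results can be called confirmatory. Option 1 gives up confirmatory claims on the other features. Option 2 lowers power per feature, to the extent shown above if a difference of 0.8 is assumed, so the sample size should be checked again at the adjusted level.
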